		**Bystander** ** Witnessed**				
**16**	**Urban or Rural**	**Rural Location**		*****	*****	*****
		**Urban Location**				
**17**	**Weekday or ** **Weekend**	**Weekend**		*****	*****	*****
		**Weekday**				
**18**	**Number of ** **Adrenaline Doses**	**Number of ** **Adrenaline Doses**				*****
**19**	**Amiodarone** ** Administered**	**Amiodarone Not ** **Administered**				*****

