### Variables and categories of concern

All analysis will be based on the variables shown in
Table 1. Variables 1–19 will be obtained from the OHCAR. Variables 20, 21 and 22 represent component time periods that are a priori considered to be potentially significant in the context of either system level developments or key population health challenges (Covid-19) during the study time period. Variables 20,21 and 22 will be dummy variables created using the ‘Year’ variable. Variables 20 and 21 will be linked dummy variables derived from the same 3-level categorical indicator of period and will be simultaneously included in regression models. We do not expect collinearity of these predictors, as transition and post-transition period correspond to years 2015 and 2016, and 2017 through 2020, respectively. The Covid period dummy variable (variable 22) will be an indicator of 2020 only, and thus should allow us to estimate any shift in survival in the final year of the study data.
Table 1 highlights the independent variables that will be explored for each outcome of interest. Where an original OHCAR variable has multiple potential associated categories, we will collapse these categories to avoid decreased statistical power from analysis of an excessive number of potentially sparse categories. Original and collapsed categories are shown in
Table 1. Season will represent the ‘winter’ healthcare period (October to March) as compared to other as ‘winter’ is a period of increased demand for the Irish healthcare service. The three time categories chosen are adopted based on previous OHCA research
^
44
^. Home (versus other) location was chosen as home represents the most common location for OHCA in Ireland. ‘Year’ (variable 9) will be treated as a continuous variable to conserve degrees of freedom and statistical power.

**Table 1. T1:** Variables for analysis.

Variable Number	Variable	Categories	Collapsed Categories	Outcome of Interest		
				Bystander CPR	Bystander Defibrillation	Survival to Hospital Discharge
**1**	**Airway** ** Management**	**Basic ** **Management**	**None of the listed devices ** **used, OPA/NPA, No advanced** ** airway**			*****

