		**Supraglottic** ** airway device**				
		**Intubation**				
**2**	**Aetiology**	**Presumed Other**	**Trauma, Respiratory, ** **Submersion, Non-cardiac, ** **Other**	*****	*****	*****

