		**Home Location**				
**7**	**Mechanical CPR**	**No Mechanical ** **CPR Provided**				*****

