		**Evening**				
		**Morning**				
**14**	**Total No of Shocks** ** Delivered**	**Total No of Shocks ** **Delivered**				*****
**15**	**Who Witnessed** ** Collapse**	**Not Witnessed**		*****	*****	*****

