		**Not Covid Period**				

### Statistical model building and interpretation procedures

For each outcome we will build a logistic model: initially a full model with all relevant predictors will be fitted. A refined model will then be built using a stepwise model selection procedure (STEPAIC function in R). This procedure builds several models from all possible combinations of the predictors by sequentially adding and dropping predictors and finally selects the model with the lowest AIC. The stepwise model will then be further improved by examining addition of pairwise interaction variables and retaining any interactions which improve fit. We will evaluate each model (full, stepwise and with interactions) based on AIC. In addition, the model deviance and a Hosmer-Lemeshow Goodness of Fit (GOF) test will be inspected for each model. To assess linearity between continuous predictors and the log odds of the outcome we will rely on good model fit as indicated by the Hosmer-Lemeshow goodness of fit test. We will also use logistic regression with higher order terms (polynomial terms) to explore if the relationship between the outcome and the continuous predictors is indeed non-linear. If higher-order terms are significant, these will be retained in the model, otherwise they will be dropped from the model. We will also attempt to ameliorate fit by including pair-wise interaction terms between predictors. We will summarise the effect of each individual variable in the final model using odds ratios and 95% confidence intervals. The effect of any significant interactions in the final model will be explored graphically. After selecting the final model from the three models, we will evaluate the predictive ability of the final best fitting model using 10-fold cross-validation and evaluate the prediction accuracy for the model.

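### In the survival model, five treatments given during the arrest stand in for resuscitation time, so their own odds ratios are biased and those for bystander CPR and the control-centre period are pulled toward 1

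*Protocol article*

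**What the plan says.** Table 1 marks five in-arrest treatments as independent variables for survival to hospital discharge, and for that outcome only:

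- variable 1, airway management (basic, supraglottic device, intubation);
- variable 7, "Mechanical CPR";
- variable 14, "Total No of Shocks" delivered, a count;
- variable 18, number of "Adrenaline Doses", a count;
- variable 19, amiodarone given or not.

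The list is closed. Under Variables and categories of concern the article states: "All analysis will be based on the variables shown in" Table 1. None of the 22 variables is resuscitation duration, time to return of circulation, or the time at which a drug, device or shock was given.

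Under Statistical model building and interpretation procedures, "initially a full model with all relevant predictors will be fitted", followed by stepwise selection on AIC and a search for interactions. Reporting is then fixed: "We will summarise the effect of each individual variable in the final model using odds ratios and 95% confidence intervals". The same survival model carries who started chest compressions (12), who gave the first shock (10) and the transition, post-transition and Covid indicators (20-22).

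**The concern.** Dose and shock counts accumulate until circulation returns or efforts stop. Mechanical CPR, an advanced airway and amiodarone become more likely the longer the arrest lasts. All five are thus partly consequences of not regaining circulation early, and survival depends heavily on regaining it. With no duration variable, the model cannot separate what a treatment does from how long the patient had been without circulation.

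Two things are at stake.

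1. **The treatment odds ratios.** AIC will tend to keep these variables because they predict well, and the plan then reports each as an effect. The article's own background (The Chain of Survival) says that drug trials suggest possible benefit in some patient groups and that airway and mechanical CPR trials showed no significant survival gain. The planned model could print apparent harm for most of these. There is a second distortion: under Emergency medical services in Ireland, only Advanced Paramedics may give intravascular drugs or intubate, so variables 18 and 19 and the intubation level of variable 1 also carry crew type, which is not in Table 1.
2. **The odds ratios the study is about.** The article hypothesises that the single control centre improved survival, and its Discussion intends the results to inform system design. If bystander CPR or the control centre works partly by bringing circulation back earlier, adjusting for consequences of late return removes part of that benefit.

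**Working it through.** The plan gives no figure to reproduce on this point, so the argument was checked by simulation.

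**Inputs from the article:** about 18,000 observations (Focus of this study); survival 6-7% (Introduction); about 20% shockable and 50% witnessed (registry section of the Introduction).

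**Assumed inputs, not in the article:**

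- Bystander CPR in 70%; Advanced Paramedic attendance in 80%.
- Time to return of circulation T is exponential with log rate = constant + 1.3 x shockable + 0.6 x witnessed + 0.4 x bystander CPR + g x post-transition, with g = 0 or 0.3.
- Efforts stop at a normal time, mean 35 and SD 8 minutes, limited to 15-60. Duration D = min(T, stop).
- Survival requires return of circulation, then logit = a + 1.2 x shockable + 0.4 x witnessed + b x (D - 10), with (a, b) = (-2.3, 0) or (-2.1, -0.05).
- Adrenaline: Poisson with mean max(D - 6, 0)/4, if an Advanced Paramedic attends.
- Shocks: 1 + Poisson(D/6) if shockable, otherwise Poisson(D/60).
- Mechanical CPR: probability 1 - exp(-max(D - 8, 0)/25). Advanced airway (yes/no): 1 - exp(-max(D - 4, 0)/12).
- Amiodarone: 80% of patients with an Advanced Paramedic and at least 3 shocks.

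No treatment appears in the survival equation, so every true treatment effect is zero. Bystander CPR and the post-transition period act only through earlier return of circulation.

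**Models:** logistic regression on shockable rhythm, witnessed, bystander CPR, transition and post-transition, without and with the five treatments; 100 replicates per scenario.

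Treatment odds ratios (true value 1), range over the four scenarios:

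| Variable | All five together | One at a time |
|---|---|---|
| Adrenaline, per dose | 0.83-0.89 | 0.76-0.86 |
| Shocks, per shock | 0.86-0.94 | 0.70-0.84 |
| Mechanical CPR | 0.48-0.64 | 0.22-0.42 |
| Advanced airway | 0.49-0.69 | 0.22-0.43 |
| Amiodarone | 1.38-1.54 | 0.45-0.68 |

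Amiodarone changes direction because shock count and adrenaline already carry duration in the joint model. Both directions are spurious.

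Other odds ratios, without -> with the five treatments:

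| b, g | Survival | Bystander CPR | Post-transition | Replicates with post-transition p<0.05 |
|---|---|---|---|---|
| 0, 0 | 6.5% | 1.35 -> 1.20 | 0.99 -> 0.99 | 4% -> 4% |
| 0, 0.3 | 7.0% | 1.33 -> 1.18 | 1.21 -> 1.11 | 79% -> 29% |
| -0.05, 0 | 6.6% | 1.41 -> 1.17 | 0.99 -> 0.99 | 3% -> 4% |
| -0.05, 0.3 | 7.2% | 1.40 -> 1.16 | 1.26 -> 1.09 | 93% -> 22% |

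Share of the log odds ratio lost:

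- Post-transition: 1 - ln(1.11)/ln(1.21) = 1 - 0.104/0.191 = 45%, and 1 - ln(1.09)/ln(1.26) = 1 - 0.086/0.231 = 63%.
- Bystander CPR: from 1 - ln(1.20)/ln(1.35) = 1 - 0.182/0.300 = 39% to 1 - ln(1.16)/ln(1.40) = 1 - 0.148/0.336 = 56%.

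The witnessed odds ratio also fell, from 2.18-2.33 to 1.80-1.88. Non-collapsibility does not explain this: adding prognostic covariates unrelated to the exposure moves a logistic odds ratio away from 1, and these moved toward it.

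The same set-up at higher survival (8.1-9.2%) gave a similar picture: bystander CPR 1.36-1.43 -> 1.18-1.23, and a real post-transition effect 1.23-1.28 -> 1.11-1.12.

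**Limits.** With 100 replicates the percentages carry a standard error of up to sqrt(0.25/100) = 5 points. The fitted models omit the linear year term, the Covid indicator, first shock and the stepwise step, so the percentages are not the power of the planned model. If bystander CPR or the control centre also acts other than through time to return of circulation, the proportional loss would be smaller.

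**The case against.** The best defence is that aim 2 is to model predictors, that models are chosen on AIC, and that the final one is judged by 10-fold cross-validation. For pure prediction, in-event variables are tolerable. That stands for prediction, but it does not cover the plan. Aims 3 and 4 examine system-level hypotheses on survival, the reporting rule speaks of effects, and the Discussion reads the results as factors that influence outcome. The Discussion's limitation is about other confounding variables in general; here the bias comes from variables that the plan itself puts in.

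The limits on scope also stand. The five variables carry no mark for bystander CPR or bystander defibrillation, so two of the three outcome models are untouched. Where no period effect exists, none is created.

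Three stronger readings are tempting and are not supported:

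- **All five will look harmful.** Amiodarone looked beneficial in the joint model, which is the kind the plan fits.
- **The benefit of bystander CPR will vanish.** A simulation with doses on a fixed clock, survival of 9-12% and adjustment for doses alone gives 0.41-0.44 per dose, and takes bystander CPR from 2.17-2.32 to 0.98-1.06. But the article gives survival of 6-7%, restricts intravascular drugs to Advanced Paramedics and plans a multivariable model. Closer to those conditions the result is attenuation.
- **First shock (10) has no meaning beside total shocks (14).** If the not-applicable category means zero shocks, comparisons with it are awkward. This is inferred from labels and was not tested, and bystander versus EMS first shock among shocked patients can still be estimated.

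**Conclusion.** The concern holds for the survival model. As written, the plan gives treatment odds ratios confounded by resuscitation time, and for drugs and intubation also by crew type. It also adjusts away part of any benefit of bystander CPR or the control centre that acts through earlier return of circulation. The direction follows from the structure of Table 1. The size does not come from the documents: under the stated assumptions, a real post-transition effect loses about 45-63% of its log odds ratio and bystander CPR about 39-56%. The risk for aim 3 is a missed or understated improvement, not a false one. Since the survival results under aims 2 to 4 rest on this model, the change should be made before analysis.

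**What to change.** - Define a primary survival model that omits variables 1, 7, 14, 18 and 19. Take from it the survival odds ratios for the period terms (20-22), bystander CPR (12) and the other pre-EMS factors.
- Describe the five treatments by year under aim 1.
- If they are wanted in a model, show them only in a labelled secondary prediction model. State that its odds ratios are not treatment effects, and give resuscitation time and Advanced Paramedic attendance as the reasons.
- Note in the text that first shock (10) and initial rhythm (11) may also be partly downstream of bystander action, so the bystander CPR odds ratio adjusted for them needs a caveat.

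This needs an edit to Table 1 and a few sentences in the model-building section, and no new data. The cost is lower apparent discrimination of the main survival model and one extra model to report if the secondary one is kept.

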		**Amiodarone ** **Administered**				
**20**	**Transition Period** ** (2015 & 2016)**	**Transition Period ** **(2015 & 2016)**		*****	*****	*****
		**Not Transition ** **Period**				
**21**	**Post Transition ** **Period (2017–2020)**	**Post Transition** ** Period ( 2017–2020)**		*****	*****	*****
		**Not Post ** **Transition Period**				
**22**	**Covid Period**	**Covid Period (2020)**		*****	*****	*****
		**Not Covid Period**				

### Statistical model building and interpretation procedures

For each outcome we will build a logistic model: initially a full model with all relevant predictors will be fitted. A refined model will then be built using a stepwise model selection procedure (STEPAIC function in R). This procedure builds several models from all possible combinations of the predictors by sequentially adding and dropping predictors and finally selects the model with the lowest AIC. The stepwise model will then be further improved by examining addition of pairwise interaction variables and retaining any interactions which improve fit. We will evaluate each model (full, stepwise and with interactions) based on AIC. In addition, the model deviance and a Hosmer-Lemeshow Goodness of Fit (GOF) test will be inspected for each model. To assess linearity between continuous predictors and the log odds of the outcome we will rely on good model fit as indicated by the Hosmer-Lemeshow goodness of fit test. We will also use logistic regression with higher order terms (polynomial terms) to explore if the relationship between the outcome and the continuous predictors is indeed non-linear. If higher-order terms are significant, these will be retained in the model, otherwise they will be dropped from the model. We will also attempt to ameliorate fit by including pair-wise interaction terms between predictors. We will summarise the effect of each individual variable in the final model using odds ratios and 95% confidence intervals. The effect of any significant interactions in the final model will be explored graphically. After selecting the final model from the three models, we will evaluate the predictive ability of the final best fitting model using 10-fold cross-validation and evaluate the prediction accuracy for the model.

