### Focus of this study

This study will examine data from the Irish Out-of-Hospital Cardiac Arrest Registry (OHCAR) to describe OHCA incidence and its care processes in Ireland over the period 2012 to 2020. We will further interrogate this data to identify key OHCAR variables that predict key outcomes. We anticipate approximately 18,000 relevant observations will be available for analysis. We will consider survival to hospital discharge, bystander CPR, and bystander defibrillation to be key outcomes of interest over the study period. We hypothesise that of the timeline of OHCA developments described above, two key developments are likely to be associated with a significant change in outcomes. Given the scale of reorganisation and centralisation of EMS control in 2015 and 2016 on the backdrop of the ongoing NAS ‘one life’ project we hypothesise that the NAS transition from a system of multiple regional independent control centres to the single national control centre (NEOC) would be associated with improvements in bystander CPR and survival to hospital discharge. In turn, given Covid-19’s detrimental effect on OHCA internationally we hypothesise that COVID-19 would be associated with significant reductions in bystander CPR, bystander defibrillation and survival to hospital discharge in Ireland.

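### An open-ended search for interactions, followed by one odds ratio per variable, can leave the period and Covid odds ratios conditional on a partner's reference level

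*Protocol article*

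**What the plan says.** The rules are in the protocol article, section Statistical model building and interpretation procedures. A full logistic model is fitted for each outcome. Then: "A refined model will then be built using a stepwise model selection procedure (STEPAIC function in R"). Next: "The stepwise model will then be further improved by examining addition of pairwise interaction variables and retaining any interactions which improve fit". The choice among the three is described so: "We will evaluate each model (full, stepwise and with interactions) based on AIC". Deviance and a Hosmer-Lemeshow test are inspected as well.

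From the final model the article promises an odds ratio with a 95% confidence interval for each individual variable, and graphs for significant interactions. Ten-fold cross-validation is applied to the final model once it has been selected.

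The candidate variables are fixed in Variables and categories of concern: "All analysis will be based on the variables shown in" Table 1. They include the two period dummies and the Covid dummy, which carry aims 3 and 4 (the control-centre transition and COVID-19).

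**The concern.** The search runs over every pair of predictors left in the stepwise model, and nothing in the text limits how many pairs may be kept. Two consequences follow.

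First, some retained interactions will be noise. The three-way comparison by AIC does not guard against this. If interactions enter only when they lower AIC, the interaction model cannot have a higher AIC than the stepwise model it came from, so it is chosen almost by construction. Cross-validation comes too late to affect that choice.

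Second, the reporting rule does not match the model. Once a period or Covid dummy is part of an interaction, its main coefficient is no longer an overall effect. The single odds ratio that would answer aims 3 and 4 then describes one level of some other variable, chosen by the search and by the coding.

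**Working it through.** The article states no expected number of interactions, so there is no figure of its own to reproduce.

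**Inputs**
- Table 1 marks 22 predictors for survival (variables 1 to 22) and 14 for each bystander outcome (2 to 6, 8, 9, 13, 15 to 17, 20 to 22).
- Three predictors have three levels (2 df): airway management, first shock delivered by, and time of day ("The three time categories chosen are adopted based on previous OHCA research"). Only time of day applies to the bystander models.
- Period coding: "Variables 20 and 21 will be linked dummy variables derived from the same 3-level categorical indicator of period", and "The Covid period dummy variable (variable 22) will be an indicator of 2020 only". Hence 20×21 and 20×22 are empty, and 21×22 and Year×22 are aliased with variable 22. Four pairs drop out.

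**Retention probability under AIC.** A term with d df lowers AIC when its likelihood-ratio chi-square exceeds 2d. Under the null:
- P(χ²₁ > 2) = 0.1573
- P(χ²₂ > 4) = 0.1353
- P(χ²₄ > 8) = 0.0916

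These do not depend on sample size, so the size of the registry ("We anticipate approximately 18,000 relevant observations will be available for analysis") is no protection.

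**Expected chance retentions, all predictors kept, no true interaction**
- Survival: 22×21/2 = 231 pairs, less 4 = 227, of which 167 have 1 df, 57 have 2 df and 3 have 4 df. 167×0.1573 + 57×0.1353 + 3×0.0916 = 26.3 + 7.7 + 0.3 = 34.3.
- Each bystander model: 14×13/2 = 91 pairs, less 4 = 87, of which 74 have 1 df and 13 have 2 df. 74×0.1573 + 13×0.1353 = 11.6 + 1.8 = 13.4.

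| Counting convention | Survival | Each bystander model |
|---|---|---|
| All pairs, 1 df each | 36.3 | 14.3 |
| True df, all pairs | 34.9 | 14.0 |
| True df, four pairs dropped | 34.3 | 13.4 |
| Variables 20 and 21 as one 3-level factor | 30.9–31.1 | 11.4–11.7 |

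A null simulation of forward AIC selection (18,000 cases, 6.5% events, independent synthetic 1-df predictors, Gaussian approximation) kept on average 38 interactions with 22 predictors (5th to 95th percentile 30 to 47) and 14 with 14 predictors (9 to 18).

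**If the stepwise step drops predictors.** With k one-df predictors left, the expectation is k(k−1)/2 × 0.1573:
- k = 10: 45 pairs, 7.1
- k = 12: 66 pairs, 10.4
- k = 16: 120 pairs, 18.9
- k = 20: 190 pairs, 29.9

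**If better fit meant p<0.05.** The maxima would be 231×0.05 = 11.6 and 91×0.05 = 4.6.

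**Reach into the period terms.** Post-transition has 19 estimable partners in the survival model (16 with 1 df, 3 with 2 df). Treating pairs as independent and all null, the chance that at least one is kept is 1 − 0.8427¹⁶ × 0.8647³ = 0.96. For a bystander model (10 and 1 partners) it is 1 − 0.8427¹⁰ × 0.8647 = 0.84. With only seven one-df partners left it is 1 − 0.8427⁷ = 0.70.

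**What the reported odds ratio then means.** With a Post×Age term, the Post odds ratio at age a is exp(β_Post + β_Post×Age · a). The single value exp(β_Post) is the effect at age 0 unless age is recentred. For a Post×Year term it is the effect at calendar year 0 unless Year is recoded.

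**Gap in the graphs.** Taking significant as p<0.05 (an assumption), a null 1-df interaction with p between 0.05 and 0.157 is kept but not graphed. That is (0.1573 − 0.05)/0.1573 = 68% of those kept.

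**The case against.** The strongest reply is that the size of the problem cannot be known from the article. Interactions are added to the stepwise model, so the candidate pool may be well below 22 or 14 predictors. AIC is named for comparing the three models, not for each interaction, and the text also mentions deviance, Hosmer-Lemeshow and significance. The aims are worded as exploration, the Discussion warns about confounding, and cross-validation is planned.

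Much of this stands. A reader might infer that the plan will retain some 34 false interactions for survival and 13 or 14 for each bystander outcome. The document does not support that: those counts need every predictor to survive selection and every interaction to be null. A reader might also infer that the main odds ratios become uninterpretable. That is too strong. They become conditional and can be read with suitable coding or contrasts, and a variable in no retained interaction is not affected in this way.

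The reply does not remove the point. AIC is the only numerical selection criterion the section names. Reading better fit as lower deviance would be worse, because deviance never rises when a term is added. Cross-validation after selection does not protect the choice of model. An exploratory aim still needs an odds ratio whose meaning is known before the data are searched.

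**Conclusion.** The point holds in a limited form. The article fixes an unrestricted interaction search and a reporting rule that does not fit its result. The expected number of chance interactions is at most about 31 to 36 for survival and 11 to 14 for each bystander outcome, assuming a per-term AIC rule, no loss of predictors and no true interactions. It is lower if predictors are dropped, and at most about 12 and 5 under p<0.05. Even the smaller counts leave a substantial chance that a period term is involved.

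The lasting consequence is for aims 3 and 4: the reported Transition, Post-transition or Covid odds ratio may hold only at one level of an unplanned partner, and its confidence interval takes no account of the search. This should be changed; it does not invalidate the study.

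**What to change.** State that the period and Covid odds ratios for aims 3 and 4 come from the full main-effects model: all Table 1 predictors for that outcome, no interactions, and period terms not subject to selection. The full model is preferable to the stepwise one here because stepwise selection could drop a period term.

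Limit confirmatory interaction tests to a short list fixed in advance, with a stated criterion stricter than AIC. Which interactions and which threshold are for the investigators to choose. Label any other retained interaction exploratory, and display every retained interaction, not only the significant ones. Where an interaction model is reported, give the period effects as marginal effects or as contrasts at stated covariate values.

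The cost is a few sentences of text and no new data. The downside is that a real interaction nobody foresaw would be reported as exploratory only.

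### The 95% confidence intervals for the transition, post-transition and Covid effects make no allowance for year-to-year variation, although these exposures vary only between nine calendar years

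*Protocol article*

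**What the plan says.** The section on variables and categories states how the period exposures arise: "Variables 20,21 and 22 will be dummy variables created using the ‘Year’ variable". The periods are fixed in whole years: "transition and post-transition period correspond to years 2015 and 2016, and 2017 through 2020, respectively", which leaves 2012 to 2014 as the reference. For the pandemic, "The Covid period dummy variable (variable 22) will be an indicator of 2020 only". Calendar year also enters as a single linear term (variable 9), chosen to save degrees of freedom.

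The model-building section then says: "For each outcome we will build a logistic model: initially a full model with all relevant predictors will be fitted". That model is refined by stepwise AIC, with possible interactions and polynomial terms, and the result is reported as follows: "We will summarise the effect of each individual variable in the final model using odds ratios and 95% confidence intervals". On the amount of data, the introduction says: "We anticipate approximately 18,000 relevant observations will be available for analysis".

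The article mentions no year-level variance, overdispersion factor, clustering or serial correlation. Its only sensitivity analysis compares complete cases with multiple imputation.

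**The concern.** An ordinary logistic regression treats each patient as an independent piece of information about every coefficient. That suits age, sex or initial rhythm, which differ between patients within a year. It suits variables 20 to 22 less well, because all patients in a given year share the same value. What the data say about these terms is contained in nine adjusted yearly log-odds.

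The ordinary interval is valid for them only if each year lies on the fitted year-level line apart from binomial noise. Any other influence that moves a whole year is read as part of a period effect, with no added uncertainty. The article itself lists developments without a term of their own: the growth in community first responder groups and GP responders between 2016 and 2020, the schools CPR programme, and new support posts in 2017.

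Aims 3 and 4 are answered from these three coefficients. An ordinary fluctuation between years could therefore be reported as an effect of the single national control centre or of the pandemic.

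**Working it through.** The article states no power, standard error or interval width, so there is no figure of its own to reproduce.

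**Inputs from the article.** Nine years (2012 to 2020); about 18,000 patients; survival of 6% to 7%, taken as p = 0.065; the coding of the periods.

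**Assumptions.** An even split, m = 18,000 / 9 = 2,000 cases a year; bystander CPR at 60% (no rate is given); a between-year SD on the logit scale, τ, from 0 to 0.10 (not given, so a range is shown). Patient covariates and stepwise selection are left out.

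**Step 1: year-level design.** The columns are intercept, linear Year, transition, post-transition and Covid. The 9 × 5 matrix X has rank 5, which leaves 9 − 5 = 4 residual degrees of freedom. The diagonal elements c of (X′X)⁻¹ are 2.222 (transition), 6.222 (post-transition) and 2.222 (Covid).

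**Step 2: naive standard errors.** The variance of one yearly log-odds is 1/w, with w = m·p·(1 − p).
- Survival: w = 2,000 × 0.065 × 0.935 = 121.55.
- Naive SE = √(c/w): √(2.222/121.55) = 0.135 for transition and for Covid, and √(6.222/121.55) = 0.226 for post-transition.
- Bystander CPR: w = 2,000 × 0.6 × 0.4 = 480.

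**Step 3: add between-year variation.** The yearly variance becomes 1/w + τ², so each SE is multiplied by k = √(1 + τ²w). The true type I error of a nominal 5% test is 2·[1 − Φ(1.96/k)].

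| τ | Survival: k | Type I error | Post-transition SE | Bystander CPR: k | Type I error |
|---|---|---|---|---|---|
| 0 | 1.00 | 5% | 0.226 | 1.00 | 5% |
| 0.03 | 1.05 | 6% | 0.238 | 1.20 | 10% |
| 0.05 | 1.14 | 9% | 0.258 | 1.48 | 19% |
| 0.10 | 1.49 | 19% | 0.337 | 2.41 | 42% |

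For scale, multiplying τ by p(1 − p) shows that τ = 0.05 is about 0.3 percentage points of survival or 1.2 points of bystander CPR; τ = 0.10 is about 0.6 and 2.4 points.

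**Step 4: do the remedies work?** Both were simulated over τ = 0 to 0.10.
- Scaling the SE by √(χ²/4) when χ²/4 exceeds 1, with the multiplier 1.96, gives a type I error of about 4% to 9% for survival and 4% to 12% for bystander CPR.
- Regressing the nine yearly log-odds on the year-level terms, with residual variance estimated and t on 4 degrees of freedom, gives about 5% throughout.

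**The case against.** The strongest reply is that τ is unknown. Adjustment for age, aetiology, season, response interval, initial rhythm and the rest may absorb much of the variation between years, and at τ = 0 the planned intervals are correct. This stands. A reader might infer from the design alone that the intervals are definitely too narrow, or that 42% is the expected error rate. The article supports neither: 42% combines the largest τ shown with an assumed outcome rate. For survival at small τ the error is only 6% to 9%. What does not follow is that zero may be adopted without a check, since the study's own data can test it.

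Second, the four residual degrees of freedom are not fixed by the plan. A retained polynomial in Year would leave fewer, and stepwise selection could drop a year-level term and leave more. This also stands, and the fix has to follow the final model.

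Third, the article names no variance estimator, and a fuller plan might. That is fair, but the ordinary variance is the natural reading of a logistic model with odds ratios and 95% intervals. The planned checks do not fill the gap: Hosmer-Lemeshow groups patients by predicted risk, not by year, and the deviance of individual binary data does not test scatter between years.

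Fourth, the aims are exploratory and the discussion concedes that confounders may drive the associations. The introduction nevertheless states directional hypotheses, and the concession concerns bias, not interval width.

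Last, year-level t intervals cost precision. If τ is 0, the post-transition odds ratio for survival detectable with 80% power rises from about 1.88 to about 2.34. This is a good reason not to impose them as the main analysis.

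**Conclusion.** The point holds in conditional form. The structure is certain: three exposures fixed by calendar year, one of them a single year, are analysed by a patient-level model with no stated allowance for variation between years. The direction is certain too: any variation left after case-mix and trend makes the intervals for aims 3 and 4 too narrow, never too wide. The size is not established. The ranges of 5% to 19% (survival) and 5% to 42% (bystander CPR) rest on an even 2,000 cases a year, no covariates, linear Year with all three period terms kept, the assumed 60% rate and the assumed range of τ. Point estimates and the intervals of patient-level predictors are not in question. This is a worthwhile, inexpensive improvement, not a fatal flaw.

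**What to change.** For each outcome:

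1. Compare the final model with the same model refitted with Year as nine categories. Report the lack-of-fit chi-square on its residual degrees of freedom: 4 with linear Year and all three period terms, fewer if a polynomial Year term is kept, more if a year-level term is dropped.
2. Multiply the standard errors of the period terms by √(χ²/df) when this exceeds 1.
3. As a sensitivity analysis, report the two-step estimate: nine adjusted yearly log-odds regressed on the year-level terms, with t on the residual degrees of freedom. It holds 5% where scaling alone may not.
4. Leave the intervals of patient-level predictors unchanged.
5. State that no variance method can separate Covid from another shift specific to 2020.

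The cost is wider intervals for the period terms (with 4 degrees of freedom the two-step multiplier is 2.78 instead of 1.96) and some extra work across three outcomes and the imputed datasets. No new data are needed.
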